## Abstract

**Background:** People living with Mild Cognitive Impairment (MCI) and Vascular Cognitive Impairment (VCI) are persons who do not fulfill a diagnosis of dementia, but who have a high risk of progressing to a dementia disorder. The most recent guidelines to counteract cognitive decline in MCI/VCI subjects suggest a multidimensional and multi-domain interventions combining cognitive, physical, and social activities. The purpose of this study is to test an innovative service that provides a multi-dimensional tele-rehabilitation program through a user-friendly web application. The latter has been developed through a participatory design involving MCI specialists, patients, and their caregivers. Particularly, the proposed tele-rehabilitation program includes cognitive, physical, and caregiver-supported social activities. The goal is to promote and preserve an active life style and counteract cognitive decline in people living with MCI/VCI.

**Methods:**The study is a randomized controlled trial. Sixty subjects will be randomly assigned to the experimental group, who will receive the tele-rehabilitation program, or the control group, who will not receive any treatment. The trial protocol comprises three steps of assessment for the experimental group: at the baseline (T_0), after tele-rehabilitation program (T_1) and at follow-up after 12-months (T_2). Differently, the control group will be assessed twice: at the baseline and at 12-months follow-up. Both the experimental and the control group will be assessed with a multidimensional evaluation battery, including cognitive functioning, behavioral, functional, and quality of life measures. The tele-rehabilitation program lasts 8 weeks and includes cognitive exercises 3 days a week, physical activities 2 days a week, and social activities once a week. In addition, group will be given an actigraph (GENEActiv, Activisinghts Ltd., Cambridgshire, UK) to track physical and sleep activity.

**Discussion:**Results of this study will inform on the efficacy of the proposed tele-rehabilitation to prevent or delay further cognitive decline in MCI/VCI subjects. The expected outcome is to counteract cognitive decline and improve both physical functioning and quality of life.

**Ethics and Dissemination:**The study is approved by the Local Ethics Committee and registered in https://clinicaltrials.gov (NCT03383549). Dissemination will include submission to a peer-reviewed journal, patients, and healthcare magazines and congress presentations.

**Trial Registration:** ClinicalTrials.gov ID: NCT03383549 (registration date: 26/dec/2017)

**Trial Funding:** Bando FAS Salute 2014 Regione Toscana

**Version Identifier:** ver 5—16/11/2018

## Introduction

Cognitive aging can be successful or lead to impairment depending on the interplay of a manifold of influencing factors. Among these factors, we can count genetic markers, cardiovascular status, neural functional plasticity mechanisms, as well as social, cognitive, and psychological status (1). Within unsuccessful aging paths, the balance between these factors orients toward Mild Cognitive Impairment (MCI) or Vascular Cognitive Impairment (VCI). Mild cognitive impairment (MCI) is a syndrome defined as a cognitive decline which is greater than expected for individual's age and education level but that does not interfere notably with activities of daily life (2). Since his definition in 1999 (3), MCI has been considered the transitional status between normal aging and the diagnosis of a mild dementia (4). MCI is consistently shown to have a high risk of progression to dementia (2, 5) and a pronounced risk of disability and loss of autonomy (6, 7). In addition, cerebrovascular disease that causes brain infarctions becomes more common with advancing age and represents a risk factor for the further development of vascular dementia (8, 9). The construct of VCI, a high-risk phenotype for the development of vascular dementia, has been introduced to capture the entire spectrum of cognitive disorders associated with all forms of cerebral vascular brain injury. There is evidence that about one third of dementia cases globally are attributable to potentially modifiable risk factors that include different daily habits (10, 11). Furthermore, in the study of successful aging compared to the pathological one, the fundamental role that the environment plays in counteracting cognitive decline through the activation of neuro-plasticity mechanisms for the recovery of alternative pathways has been demonstrated (12). Within a holistic framework, the adoption of an appropriate habits alongside cognitive training and enhancement activities can therefore activate brain compensation mechanisms to tackle the physiological and pathological neurodegeneration processes of the elderly, keeping the cognitive level high. On the one hand, there is rising evidence that cognitive training programs are effective in improving or at least maintaining cognitive performance and slowing the progression from MCI or VCI to mild dementia (13, 14). On the other hand, the importance of an intervention that takes into account, beside cognition, also of motor aspects in pre-clinical conditions and in the early stages of dementia has been highlighted (15). To maintain physical abilities and counteract the damage caused by the general physiological decline in the elderly, the adapted physical activity (APA) program has been recognized as an effective tool (16). Furthermore, from a holistic point of view, although social stimulation is often neglected in interventions, recent studies observed that being engaged in social activities represents a protective factor against cognitive decline (17). Therefore, promoting support from the caregivers in social activity participation has been recommended to retain the present abilities and sense of well-being in the persons with cognitive impairment (18). In line with this perspective, the most recent guidelines for the management of MCI/VCI suggest the importance of promoting multidimensional and multi-domain interventions. A multi-dimensional training program integrates different activities, such as the physical and the cognitive one. In addition, the latter could be multi-domains, including exercises that stimulate multiple cognitive domains (i.e., memory, attention, processing speed) (3, 7, 19). Finally, there is evidence that mental, physical, and social stimulation activities equally contribute to decrease dementia risk (20). How to include these activities in a feasible and sustainable rehabilitation service and how to deliver the latter to people living with MCI/VCI, still remains a debated issue. The advancement in technology has enhanced the possibility to provide remote tele-rehabilitation services through low-cost devices, that can ensure continuity of care and can easily reach people living in geographical remote areas. In fact, this kind of services supplies distant support, information exchange between patients and their clinical providers and promotes the administration of multi-dimensional activity programs (21, 22). The lack of familiarity with the technologic devices may constitute a limit to the implementation of technology enhanced services to supply a home-based tele-rehabilitation in people with advanced age or early cognitive impairment (23). For this reason, the development of an accessible service represents a design priority. The use of a participatory co-design process that follows an iterative development model might help in overcoming this limitation (24). The main aim of the proposed trial is to test the performance of a multi-dimensional tele-rehabilitation customized program, which contents are available by a user-friendly web application developed through a participatory design (involving patients, clinicians, technicians, and caregivers). The presented study would investigate whether subjects living with MCI/VCI condition participating in the tele-rehabilitation program will show improvements in cognition, quality of life, adherence, and engagement in the program with respect to subjects living with MCI/VCI condition of the control group.

## Methods and Analysis

### Study Design

The proposed study is a randomized controlled clinical trial. A Consolidated Standards of Reporting Trials (CONSORT) flow diagram for enrollment and randomization in the GOAL study is showed in Figure 1. Subjects that, at the first screening will be deemed as eligible, according to the inclusion criteria, will undergo a baseline assessment (T_0). During the baseline a general cognitive and physical evaluation will be performed by using the scales, tests and questionnaires reported in the Participant's evaluation sub-paragraph. Participants will be then randomly assigned, through the use of a computer algorithm (http://www.graphpad.com/quikcalcs/randMenu/) to the control or treatment group. The tele-rehabilitation program will comprise the performing of cognitive exercises 3 days a week, APA activities 2 days a week, and social activities once a week. In addition, treatment group will be given an actigraph (GENEActiv, Activisinghts Ltd., Cambridgshire, UK) to track physical and sleep activity. Those subjects will undergo a post-training assessment immediately at the end of the tele-rehabilitation program (T_1) and after 12 months (T_2). Participants belonging to the control group will be evaluated only at T_2.

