### Eligibility Criteria/Participants

Participants will be recruited from the Memory Clinic of University Hospital of Careggi (Florence, Italy), and the Don Carlo Gnocchi Foundation (Florence, Italy). Inclusion criteria will be the following: (a) diagnosis of MCI due to Alzheimer's Disease (AD), according to “Research Clinical Criteria” (25) or diagnosis of Vascular cognitive impairment (VCI) according to the harmonization standards from National Institute for Neurological Disorders and Stroke and the Canadian Stroke Network (8) (Table 1); (b) Mini Mental State Examination (MMSE) ≥24 (26); (c) aged 65–80 years old; (d) school attendance ≥3 years (to avoid both cultural bias and limits due to the neuropsychological instruments used); (e) right-handed according to the Edinburgh Scale (27). Exclusion criteria will be: (a) severe auditory and/or visual loss; (b) severe behavioral/psychiatric disturbances; (c) actual or anamnestic substance abuse disorder; (d) cognitive disturbances secondary to an acute or general medical disorders (e) stable medication of the following pharmacological treatments: cholinesterase inhibitor, memantine, antidepressant, or antipsychotic drugs.

**Table 1 T1:** Criteria for MCI/VCI classification.

**MCI due to AD**	**VCI**
•Hachinski ischemic score ≤ 4 •Exclusion of other dementia-causes with cerebral TC or MRI •Fazekas score < 2 •Biomarkers of neuronal injury (Rate of brain and hippocampal atrophy, FDG-PET imaging or CSF tau/phosphorylated-tau) OR •Biomarker of β amyloid deposition (CSF Ab42 ore PET amyloid imaging) compatible with MCI due to AD	•Hachinski ischemic score >4 •Fazekas score ≥2 •MRI or TC evidence of (one or more): - Multiple white matter lesions compatible with small vessel disease - Lacunar state - One or more ischemic lesions in strategic areas

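### The trial pools two diagnoses known before randomisation, but the stated two-sample comparison at T_2 has no diagnosis term and no stratification by diagnosis is described

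*Protocol article*

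**What the plan says.** The Eligibility Criteria/Participants section admits two diagnoses: "diagnosis of MCI due to Alzheimer's Disease (AD), according to" research criteria, "or diagnosis of Vascular cognitive impairment (VCI) according to the harmonization standards" that the section cites. Table 1 separates them by Hachinski score (at most 4 against above 4), by Fazekas score (below 2 against 2 or more), and by biomarkers against vascular imaging findings. Diagnosis is an inclusion criterion, so it is fixed before allocation.

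The Study Design section describes allocation in one sentence: "Participants will be then randomly assigned, through the use of a computer algorithm", followed by the address of a web tool and "to the control or treatment group". No stratification, blocking, minimisation or allocation ratio is mentioned. The Abstract gives the total as sixty.

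The Statistical Analyses section compares changes in primary and secondary outcomes between arms with an independent-samples test chosen according to normality. No covariate or stratifying factor is named. The Outcomes Measures section sets this comparison on change from T_0 to T_2 in the whole sample. The Sample Size section claims power above 70% at an alpha of 0.05 with 60 subjects.

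**The concern.** The introduction links MCI to progression to dementia in general and VCI to vascular dementia in particular. If the two groups change at different rates over 12 months, diagnosis contributes variance to the change scores. A two-sample test leaves all of that variance in the error term. Nor does it correct for an uneven split of the diagnoses between arms, which is not rare with sixty participants and unstratified allocation.

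Precision and credibility are at stake. Planned power is only just above 70%, and the discussion itself concedes that the sample is small. A visible imbalance in diagnosis would invite doubt about the result, and the stated test offers no answer to it.

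The point does not depend on how allocation was done. If it is unstratified, nothing in the stated comparison handles an imbalance. If it is stratified by diagnosis, a test that ignores the strata is conservative whenever diagnosis predicts outcome.

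**Working it through.** **Inputs**
- From the article: 60 participants, two diagnoses, alpha 0.05, power above 70%, two-sample test.
- Assumed because not stated: 30 per arm, two-sided test, 12 to 30 of the 60 in the smaller diagnosis group, and the difference δ in 12-month change between diagnoses, in within-diagnosis SD units.

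**1. The plan's own power figure.** No effect size or SD is given, so the claim can only be solved backwards. The standard error of the arm difference is √(2/30) = 0.258 SD. The difference detectable with 70% power is (1.960 + 0.524) × 0.258 = 0.64 SD two-sided, or 0.56 SD one-sided. At 0.65 SD, power is 71.1% by the normal approximation and 69.7% by the exact t. The claim is attainable but cannot be verified.

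**2. Chance of imbalance if allocation is unstratified.** Let K be the size of the smaller diagnosis group and X the number of them in one arm. X is hypergeometric (60, K, 30), and the difference in diagnosis share is |2X − K|/30. The chance of 20 points or more is:

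| Mix | Probability |
|---|---|
| 30/30 | 19.6% |
| 24/36 | 18.7% |
| 20/40 | 17.0% |
| 18/42 | 15.8% |
| 15/45 | 7.2% |
| 12/48 | 10.4% |

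The figures are uneven because |2X − K| has the same parity as K: with odd K the first value at or above 20 points is 7/30, or 23.3 points. Among all K from 12 to 30, only 13/47 falls below 7%, at 5.8%. For a simple coin-toss sequence the chances are 15.5% (30/30), 12.1% (20/40) and 8.7% (15/45).

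**3. Size of the shift.** A 20-point imbalance moves the unadjusted difference by 0.20 × δ. For δ from 0.2 to 1.0 this is 0.04 to 0.20 SD, against a standard error of 0.258 SD and a detectable difference of 0.64 SD. Across all possible allocations with a 30/30 mix, the SD of the difference in share is 0.130, so the typical shift is 0.130 × δ, or 0.03 to 0.13 SD.

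**4. Variance left in the error term.** With diagnosis share p, the proportion of outcome variance due to diagnosis is p(1 − p)δ² / (1 + p(1 − p)δ²). At p = 0.5 this is 0.01/1.01 = 1% for δ = 0.2, 0.0625/1.0625 = 6% for δ = 0.5, and 0.25/1.25 = 20% for δ = 1.0.

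**5. Power with diagnosis in the model.** The unadjusted signal-to-noise ratio at 70% power is 1.960 + 0.524 = 2.484. Adjustment divides it by √(1 − R²).
- R² = 1%: 2.484/0.995 = 2.497, power Φ(0.537) = 70.4%.
- R² = 5%: 2.484/0.975 = 2.549, power Φ(0.589) = 72.2%.
- R² = 20%: 2.484/0.894 = 2.778, power Φ(0.818) = 79.3%.

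Under unstratified allocation, adjustment has a small price. The expected squared correlation between arm and diagnosis is 1/59 = 1.7%, which raises the variance by a factor of about 1.017. Power is then 69.7% at R² = 1% and 78.6% at R² = 20%, still about 70% to 79%.

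**6. Effect of stratified blocks.** In 4,000 simulated allocations per mix, with blocks of 4 stratified by diagnosis, no imbalance reached 20 points. The largest was 6.7 points for 30/30, 0 for 20/40 and 3.3 for 15/45.

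**The case against.** The strongest objection is that this is a condensed journal article. Strata and block sizes are details that such articles commonly leave to the full protocol, and the flow diagram of enrolment and randomisation is not shown. A reader might infer that the allocation is unstratified. The text does not say so, and the named tool could be run separately within each diagnosis. This stands, so the imbalance figures are conditional. It does not dispose of the analysis, because the article does name the test, and the test named has no diagnosis term.

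A reader might also infer that one diagnosis declines faster. No section says this. The introduction describes both conditions as high risk, both groups meet the same MMSE and age limits, and Table 1 separates cause rather than rate of change. The test is on changes, so a difference in baseline level alone would largely cancel. This stands too: δ is an assumption, and at its low end the gain from adjustment is nil.

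A third tempting reading is that chance imbalance biases the comparison. It does not. Averaged over allocations, the randomised test is unbiased and keeps its type I error. The shifts in step 3 describe single realised allocations.

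A fourth is that stratified blocks would cure the problem at no cost. They leave small imbalances. Controls receive no treatment, so allocation is visible and blocks are easier to predict than simple randomisation. Blocks alone would also not recover the lost precision; the model term does that.

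Finally, the two recruiting clinics add nothing here. No clinic effect is given, assessments take place at one centre, and the programme is delivered at home.

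**Conclusion.** The point holds as a worthwhile improvement to a stated method, not as a flaw that invalidates the trial. The primary T_2 comparison pools two diagnoses known at baseline and, as written, takes no account of them. If allocation is unstratified and 1:1, a diagnosis imbalance of 20 points or more has a chance of about 7% to 20%, depending on a mix that the article does not give. The consequence is lost precision and credibility, not bias. If diagnosis explains 1% to 20% of outcome variance, a range that is assumed and not drawn from the article, adjustment takes 70% power to between about 70% and 79%. Adjustment carries the recommendation; stratification is conditional on how allocation is actually done.

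**What to change.** For the primary T_2 comparison, replace the unadjusted two-sample test with a linear model of change that includes treatment and diagnosis (MCI due to AD or VCI). The cost is one degree of freedom and no extra participants. It can be adopted whether or not enrolment has started, preferably before any outcome data are examined by arm.

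State the allocation ratio and whether allocation is stratified by diagnosis. If it is not and enrolment is still open, stratify the remaining allocations by diagnosis with concealed blocks of varying size. This means two lists instead of one, somewhat greater predictability in an open-label trial (reduced but not abolished by concealment and varying sizes), and a small residual imbalance. If enrolment is complete, the model term alone is enough.

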**Figure 1 F1:**
[figure not shown]
CONSORT flow diagram. Consolidated Standards of Reporting Trials (CONSORT) flow diagram for enrollment and randomization GOAL study.

### Eligibility Criteria/Participants

Participants will be recruited from the Memory Clinic of University Hospital of Careggi (Florence, Italy), and the Don Carlo Gnocchi Foundation (Florence, Italy). Inclusion criteria will be the following: (a) diagnosis of MCI due to Alzheimer's Disease (AD), according to “Research Clinical Criteria” (25) or diagnosis of Vascular cognitive impairment (VCI) according to the harmonization standards from National Institute for Neurological Disorders and Stroke and the Canadian Stroke Network (8) (Table 1); (b) Mini Mental State Examination (MMSE) ≥24 (26); (c) aged 65–80 years old; (d) school attendance ≥3 years (to avoid both cultural bias and limits due to the neuropsychological instruments used); (e) right-handed according to the Edinburgh Scale (27). Exclusion criteria will be: (a) severe auditory and/or visual loss; (b) severe behavioral/psychiatric disturbances; (c) actual or anamnestic substance abuse disorder; (d) cognitive disturbances secondary to an acute or general medical disorders (e) stable medication of the following pharmacological treatments: cholinesterase inhibitor, memantine, antidepressant, or antipsychotic drugs.

**Table 1 T1:** Criteria for MCI/VCI classification.

**MCI due to AD**	**VCI**
•Hachinski ischemic score ≤ 4 •Exclusion of other dementia-causes with cerebral TC or MRI •Fazekas score < 2 •Biomarkers of neuronal injury (Rate of brain and hippocampal atrophy, FDG-PET imaging or CSF tau/phosphorylated-tau) OR •Biomarker of β amyloid deposition (CSF Ab42 ore PET amyloid imaging) compatible with MCI due to AD	•Hachinski ischemic score >4 •Fazekas score ≥2 •MRI or TC evidence of (one or more): - Multiple white matter lesions compatible with small vessel disease - Lacunar state - One or more ischemic lesions in strategic areas

### Participants' Evaluation

Participants will be assessed through an extensive evaluation including cognitive functioning, behavioral, functional and perceived quality of life measures with the following tests (Table 2):
The Montreal cognitive assessment [MoCA; (28)], which represents a sensitive tool in persons with MCI for a general cognitive assessment;The Digit span and the Corsi span tasks (backward and forward) (29), to assess both verbal and visuo-spatial short-term memory and working memory;The Free and Cued Selective Reminding Test [FCSRT; (30)] -Delayed Free Recall (DFR) and Immediate Free Recall (IFR) for verbal episodic memory evaluation;The Rey Complex Figure Test, copy and delayed recall [RCFT; (31)], to evaluate constructional skills, visuographic memory and some aspects of planning and executive function;The modified card sorting Test, short version [MCST; (32)] for the assessment of executive functions;The Trail Making Test [TMT; (33)] for the assessment of attention and -executive functions;The Stroop test, short version (34), to assess selective attention, cognitive flexibility and sensitivity to interference;The Semantic and Fonemic fluencies (35, 36) or the assessment of language skills;The Activities of Daily Living Inventory [ADCS/ADL; (37)] to assess patient's performance in the basic and instrumental activities of daily living.The center for Epidemiological Studies Depression scale [CES-D; (38)] to evaluate both the presence and the entity of depressive symptoms;The 36-Item Short Form Survey [SF-36; (39)] to assess the subjective perceived quality of live;The cognitive Reserve Index questionnaire [CRIq; (40)] for the evaluation of the cognitive reserve;The Short physical performance battery [SPPB; (41)], to measure functional status and physical performance;The Harvard Alumni Activity Survey [HAAS; (42)], to assess physical activity level;The International Physical Activity Questionnaire – Short Form [IPAQ; (43)], for health related physical activity evaluation.

**Table 2 T2:** Evaluation battery during the proposed trial.

**Outcome measures**	***T_0***	***T_1***	***T_2***
